## Abstract

**Background:**

Despite long-term or permanent health problems, cancer survivors are often motivated to return to work. For cancer survivors who have lost their job, return to work can be more challenging compared to employed survivors, as they generally find themselves in a more vulnerable social and financial position. Cancer survivors with job loss may therefore be in need of tailored return to work support. However, there is a lack of return to work intervention programs specifically targeting these cancer survivors. The number of cancer survivors with job loss in developed countries is rising due to, amongst others, increases in the incidence and survivor rate of cancer, the retirement age and the proportion of flexible employment contracts. Hence, we consider it important to develop a tailored return to work intervention program for cancer survivors with job loss, and to evaluate its effectiveness compared to usual care.

**Methods/Design:**

This study employs a two-armed randomised controlled trial with a follow-up period of 12 months. The study population (n = 164) will be recruited from a national sample of cancer survivors (18–60 years), who have been sick-listed for 12–36 months. Participants will be randomised by using computerized blocked randomisation (blocks of four). All participants will receive usual care as provided by the Dutch Social Security Agency. Additionally, participants in the intervention group will receive a tailored return to work intervention program, which includes vocational rehabilitation and supportive psychosocial components, as well as (therapeutic) placement at work. The primary outcome measure is duration until sustainable return to work; the secondary outcome measure is rate of return to work. Other parameters include, amongst others, fatigue, coping strategy and quality of life. We will perform Cox regression analyses to estimate hazard ratios for time to sustainable return to work.

**Discussion:**

The hypothesis of this study is that a tailored approach for cancer survivors with job loss is more effective, regarding return to work, compared to usual care. The results of this study will provide insight into the ways in which return to work can be facilitated for cancer survivors with job loss.

**Trial registration:**

Netherlands Trial Register: NTR3562.

## Background

Cancer is increasingly perceived as a chronic disease with long-term or permanent health problems [1-3]. Multiple studies report cancer survivors (CSs) to experience, for example, fatigue, depression or functional impairments long after treatment has been completed [4-6]. As a result, CSs’ quality of life, daily functioning and labour participation may be affected [7,8]. With regard to labour market participation, studies have shown that CSs are often motivated to return to work (RTW) and that they attribute positive effects to work. That is, CSs have reported that work enables them to regain a sense of normalty and control [9]. Also, RTW reduces avoidable work disability, thereby decreasing the risk of financial loss for both CSs and society [10].

A recent review found that circa 62% of CSs return to work within 12 months of sick leave. Although the majority of CSs eventually returns to work, still a considerable group of CSs does not resume work. Multiple reasons have been reported for CSs not returning to work, most of which can be categorized as cancer-related, psychosocial-related or work-related [11]. Specifically, work-related factors, such as absence of an employment contract, may create barriers for RTW of CSs. For persons with an insecure employment status, in general, the literature clearly shows that they experience a larger (emotional and practical) distance to the labour market, are lower educated and have an increased risk for prolonged sick leave compared to employees [12,13]. Also, in their RTW, CSs with job loss may face unique barriers, such as having to go through job application processes and compete with “healthy” workers for a job. As a result, after cancer, the RTW process for persons with job loss may be different from the RTW process in employed persons.

In the absence of an employer, CSs who have lost their job in the Netherlands may receive sickness or disability benefits from the Dutch Social Security Agency (SSA). If so, they will be supported by a SSA team, which consists of an insurance physician, a reintegration expert and a labour expert. The number of CSs that receive benefits, either temporary or permanent, has increased over the years. For instance, in 2013, 10.2% more CSs were receiving temporary disability benefits and 17.7% more CSs were receiving permanent disability benefits, compared to 2012 [14]. It is expected that the number of CSs with job loss in the occupational age will keep rising, not only in the Netherlands, but also in other Western economy countries, as a result of the increases in the incidence and survival rate of cancer [15], the retirement age [16], and the proportion of flexible employment contracts [17]. The Dutch SSA has specifically expressed a need for a tailored RTW intervention program for this target group. Current RTW programs are usually aimed at adjusting the current workplace of the CS and negotiating with the CS’s own employer. For CSs with job loss, these programs are not suitable, as they have no workplace or employer (anymore). In addition, it is important to consider that, for CSs with job loss, RTW includes job application processes and starting in a new job that comes with an unfamiliar working environment. Consequently, CSs with job loss are in need of tailored support that targets these specific barriers to RTW.

Therefore, the aim of this study is to develop a tailored RTW intervention program for CSs with job loss, and to study its effectiveness on duration until sustainable RTW in a randomised controlled trial with a follow-up period of 12 months, compared to usual care, as currently provided by the SSA.

## Methods/Design

### Design/setting

This study employs a two-armed non-blinded randomised controlled trial (RCT) with a follow-up period of 12 months. Data will be gathered using questionnaires at baseline, 3, 6 and 12 months post-study entry. Prior to the start of this study, a focus group study with CSs with job loss and/or unemployment experience was conducted, in order to explore barriers and facilitators they experienced with regard to RTW. We used the results from this focus group study to develop the intervention program that is being evaluated in this study. Design and results of the focus group study will be published separately. The CONSORT statement was used to report the design of this study [18]. The study was approved by the Medical Ethical Committee of the VU University Medical Center (VUmc) and the Scientific Committee of the EMGO+ Institute / VUmc.

### Study population

The study population consists of CSs with job loss, aged 18 to 60 years, who are registered at the SSA and who have been sick-listed and receiving sickness or disability benefits in the last 12–36 months. Within the group of CSs with job loss, registered at the SSA, three subtypes of workers can be distinguished: (1) workers whose temporary employment contract ended before or during sick leave; (2) temporary agency workers, and (3) unemployed workers, i.e., these workers had lost their job prior to their cancer diagnosis, and consequently, they received unemployment benefits. After being diagnosed with cancer, their benefits changed from unemployment benefits to sickness or disability benefits.

CSs who have lost their job will be included in this study if they have completed intensive cancer treatment (at least) six weeks prior to the start of this study (based on self-report by the CS), if their health status allows them to participate in the study (based on self-report by the CS) and if they have no comorbidities (e.g., severe psychological or physical conditions, apart from a potential cancer diagnosis) that would interfere with participating in this study (based on report from the CSs’ general practitioner (GP)). In case a CS is invited to participate, but is still receiving, or scheduled to receive, intensive (cancer) treatment (e.g., chemotherapy, radiotherapy, surgery or another type of intensive curative treatment), he/she will be wait-listed for inclusion until (at least) six weeks after completing such treatment(s). Furthermore, CSs will be excluded in case of pregnancy, lack of knowledge of the Dutch language and/or an ongoing conflict with the SSA regarding a sickness or disability benefit claim. Additionally, CSs will be excluded if they are participating, or signed up to be a participant, in a concurrent scientific study and/or re-integration or rehabilitation program aimed at RTW.

### Recruitment of participants

The process of recruitment is described below and illustrated in the participant recruitment flow diagram (Figure 1).

**Figure 1 Fig1:**
[figure not shown]
**Participant recruitment flow diagram.**

Potentially eligible participants will be recruited using the national database of the SSA, in which persons applying for sickness or disability benefits are registered. The database contains data regarding demographics, employment status, type of sickness or disability benefit and medical cause, due to which the benefits are granted. A search query will be developed to identify CSs with granted benefits due to a cancer diagnosis. An in-house SSA researcher will use the query to identify potential participants, because of privacy concerns. This SSA researcher will only be involved in this particular part of the recruitment process and in no other parts of the study. Retrospectively, the search query will be used only once to identify CSs who have been sick-listed from 12 to 36 months. Prospectively, with a frequency of twice per month, the search query will be used to identify CSs who have been sick-listed for 12 months. Prospective recruitment will continue for an estimated duration of one and a half years, until the sample size will be reached.

Potential participants will receive an information package from the SSA, which will contain an invitational letter from the chief medical officer from the SSA, a brochure with more detailed information on the study, an informed consent form in which respondents can give their consent to be contacted for information regarding the study, and a short questionnaire. The information package will also include a postcard, by which persons can respond to the researcher whether they are interested in the study or they can provide for declining participation, in case they wish not to participate. Also, on the postcard they can select the option of receiving only the baseline questionnaire, which aims to collect data for comparison between responders and non-responders. Finally, if a person is willing to participate, but only after a few weeks or months, they can select ‘contact me later’ on the postcard. Potential participants who do not return either the short questionnaire, including informed consent form, or the postcard, will receive a reminder letter after two weeks.

The short questionnaire in the information package aims to indicate whether or not the respondent is eligible for participation. Only when a respondent is clearly not eligible for participation in the study, based on this short questionnaire, the researchers will send an informational letter to thank them for their interest in the study. All other respondents will be contacted by telephone to provide additional information about the study procedures and to check if they meet the criteria for participation in the study. After the telephone call, respondents who meet the criteria will receive the baseline questionnaire and a second informed consent form, in which respondents give their consent to participate in the study. Respondents will be offered a choice between receiving the baseline and follow-up questionnaires on paper or via e-mail. If they do not return the baseline questionnaire and/or the informed consent form, then a reminder letter or e-mail will be send after two weeks. When the respondent returns the baseline questionnaire and the informed consent form, he/she will be included in the study and randomly allocated to either the intervention group or the control group. The participant’s GP and the team at the SSA will be notified of the inclusion of the participant in this study and they will receive information about the study. The participant’s file at the SSA will be labelled as ‘research participant’ to facilitate easy recognition by the SSA experts. The GP will be asked to report if the participant has any comorbidities that would interfere with participation (in the intervention program) in this study. In case the participant’s GP feels that a participant’s medical case may be unsuitable for participation in the study, the GP can contact the researchers to deliberate. If necessary, the researchers will organize a joint meeting with the GP and the research team to discuss the CS’s case and achieve consensus about participation.

All participants will be guided by their SSA team according to usual care. Additionally, participants in the intervention group will receive the tailored RTW intervention program. All participants will be asked to complete all questionnaires prior to randomisation (T0), at 3 months (T1), at 6 months (T2) and at 12 months (T3) post-study entry. If a person does not return a follow-up questionnaire, then a reminder letter or e-mail will be sent after two weeks.

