### Randomisation

Prior to randomisation, we will apply pre-stratification in our inclusion procedure to ensure equal representation of the three subtypes amongst CSs with job loss in our sample; (1) workers whose temporary employment contract ended before or during sick leave; (2) temporary agency workers; and (3) unemployed workers. Randomisation to either the intervention group or control group will be performed on the individual level and will be performed separately for each stratum. Randomisation will be performed by the coordinating researchers (with the exception of the executive researcher), using computerized blocked randomisation by means of the Randomisation Plan Generator [44]. The number of participants in each block will be four, with an allocation ratio of 1:1.

Blinding to the randomisation outcome in this study is not possible due to the nature of the intervention program, in which various stakeholders will need to cooperate to support and guide participants in the intervention group. Furthermore, for practical reasons with regard to usual care, the researchers will have to inform the SSA team and the GP of participants about the inclusion of the participant and the group to which the participant was randomised.

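### As written, the GP comorbidity report that decides eligibility is sought after randomisation, and nothing keeps the GP unaware of the arm, so allocation-aware exclusion is possible

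*Protocol article*

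**What the plan says.** Four sections of the protocol article bear on this.

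- **Study population.** Completion of treatment and general health status are judged by self-report. Comorbidity is different: survivors enter "if they have no comorbidities" of a kind "that would interfere with participating in this study (based on report from the CSs’ general practitioner (GP").
- **Recruitment of participants.** When the baseline questionnaire and second consent form come back, "he/she will be included in the study and randomly allocated to either the intervention group or the control group". The next sentence reads "The participant’s GP and the team at the SSA will be notified of the inclusion of the participant in this study". Then: "The GP will be asked to report if the participant has any comorbidities that would interfere with participation (in the intervention program"), and the sentence ends by tying this to participation in the study. A GP with doubts can contact the researchers, and a joint meeting may be held to "discuss the CS’s case and achieve consensus about participation".
- **Randomisation.** The researchers must "inform the SSA team and the GP of participants about the inclusion of the participant and the group to which the participant was randomised". The section does not say whether this happens before or after the GP's comorbidity report.
- **Statistical analysis.** All analyses follow intention to treat, with a per-protocol analysis if necessary. The section does not mention participants judged unsuitable after randomisation.

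**The concern.** An eligibility criterion should be settled before allocation exists. Here the criterion appears to be assessed once the participant has an arm, by a GP who may know that arm, with a research team that is not blinded either.

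The wording of the question adds to the risk. A control participant has no program for a comorbidity to interfere with, so a GP who knows the allocation has a practical reason to object more often in the intervention arm. Those objected to would plausibly be sicker and less likely to return to work. If they then stopped returning questionnaires, the main source of the primary outcome, or were left out of the analysis, the intervention arm would look faster for reasons unrelated to the program.

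**Working it through.** **Order of events.** The criterion in Study population rests on the GP's report. In Recruitment, the screening steps before allocation are the short questionnaire and the telephone call, and both involve only the respondent. Inclusion and random allocation follow on return of the forms. The GP first appears in the next sentence, notified of an inclusion already made and then asked about someone already called a participant. No sentence in the article places the GP report before allocation.

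**The plan's own sample size.** Inputs from Sample size: HR 2, half returning within 12 months, power 0.80, two-sided alpha 0.05, 20% loss.
- Schoenfeld events = 4(1.96 + 0.84)² / (ln 2)², which rounds up to 66. 66 / 0.5 = 132, against 130 stated; 65 events give power 0.798.
- 65 / 0.8 = 81.25, so 82 per arm and 164 in total, as stated.

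The sample size reproduces and is not affected. The point concerns bias.

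**Illustration 1: simple formula.** Let S be the control proportion not returned at 12 months. Under HR 2 the intervention proportion is S². Half returning overall means (1 − S) + (1 − S²) = 1, so S + S² = 1, S = 0.618, and control return to work is 38.2%. Now suppose the program does nothing, and remove *ex* people with return chance *r* from the intervention arm only:

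p = (82 × 0.382 − ex × r) / (82 − ex); apparent HR = ln(1 − p) / ln(0.618)

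Example: ex = 8, r = 0 gives p = 31.32 / 74 = 0.423 and HR = 1.14.

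| Removed of 82 | r = 0 | r = 0.10 |
|---|---|---|
| 4 | 1.07 | 1.05 |
| 8 | 1.14 | 1.11 |
| 12 | 1.23 | 1.17 |

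**Illustration 2: Cox limit.** True HR is 1, with 50% return in the full population. A share s has a poor prognosis (12-month return r) and the rest return at (0.5 − s·r)/(1 − s), with exponential times within each class. The poor-prognosis share is removed from the intervention arm only. The log HR solves the large-sample Cox score equation. Type I error is Φ(d − 1.96) + Φ(−d − 1.96), where d = |ln HR| × √(D·a(1 − a)), D is the expected number of events starting from 82 per arm, and a = (1 − s)/(2 − s).

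| Share removed | r = 0.25 | r = 0.10 | r = 0 |
|---|---|---|---|
| 5% (about 4) | HR 1.04, error 0.053 | 1.06, 0.058 | 1.08, 0.062 |
| 10% (about 8) | 1.08, 0.064 | 1.13, 0.085 | 1.16, 0.104 |
| 15% (about 12) | 1.13, 0.084 | 1.21, 0.137 | 1.26, 0.185 |

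With 65 per arm the type I error is slightly lower, at most 0.156 in this table. If the same share of equally ill people left both arms, the HR would be 1.00.

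**The case against.** A reader might draw three stronger conclusions, and the document supports none of them.

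- *That the rule is asymmetric by design.* The question is put for every participant, its sentence ends by referring to the study, and the next sentence speaks of suitability for the study. The program appears only in a parenthesis. Uneven use between arms is a plausible inference, not a stated rule.
- *That the step contradicts intention to treat.* No section says that a participant flagged by the GP leaves follow-up or the analysis set. The consensus meeting could end with the person still followed and analysed as allocated. The two sections are unreconciled, not contradictory.
- *That the order is stated outright.* It is read from the sequence of sentences and from the GP being notified of an inclusion. Figure 1, which illustrates recruitment, was not available for this check, and the timing of the disclosure of the arm relative to the report is not given.

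The size can also be challenged, and rightly. The document gives no number of GP exclusions, no split by arm and no return rate among those excluded. Earlier screening may leave few cases; at about 4 removals the type I error is close to nominal, and any removals from the control arm would offset the shift.

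What stands is narrower. A criterion that the protocol assigns to the GP is, on its own wording, collected after allocation, with no safeguard against knowledge of the arm. When eligibility is assessed is a trial procedure that this article itself describes, so it cannot simply be left to an analysis plan.

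**Conclusion.** The point holds as a permitted route to bias, not as a demonstrated one. Study population and Recruitment disagree on whether the GP criterion is met before or after entry, and Randomisation leaves the GP free to know the arm when reporting. If exclusions followed, fell mainly on the intervention arm and took people out of follow-up or analysis, the bias would favour the program.

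Under no true effect and removals from that arm only, the apparent HR would be about 1.04 to 1.08 for about 4 removals of 82 and up to about 1.26 for about 12, with two-sided type I error from about 0.05 to 0.19. The upper end needs about 15% of one arm removed, none of the other, and no return to work among those removed. Nothing in the document makes that likely. The planned 164 is unaffected. The reason to act is that comparability lost after randomisation cannot be restored in the analysis, while the remedy is cheap.

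**What to change.** 1. In Recruitment, obtain the GP comorbidity report after consent is received and before randomisation, with a fixed waiting period after which a non-reply is handled by a rule stated in advance. Bring Study population, Figure 1 and Randomisation into line, so that the GP learns the arm only after reporting.
2. Word the question identically for everyone, as participation in the study, without reference to the program.
3. In Statistical analysis, state that everyone randomised is followed and analysed in the allocated group whatever the GP later reports.
4. If some participants have already been randomised under the present order, report by arm the number for whom participation was reopened after allocation and the outcome of each case.

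The cost is a short delay before randomisation and a reordered GP letter. No extra participants or measurements are needed.

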### Tailored RTW intervention program

The intervention program was developed as a tailored RTW program in which participants, together with a RTW coach, will decide which needs should be addressed for the participant to RTW. The program was developed by the researchers in cooperation with the Dutch SSA and a national re-integration agency. In the developmental process of the program, we took results from previous studies on RTW for CSs into account [19-21]. For example, this tailored RTW intervention program contains a multidisciplinary approach towards RTW, as the literature showed that multidisciplinary RTW interventions for CSs may be more effective compared to monodisciplinary interventions or usual care [20,21]. Furthermore, we obtained advice from important stakeholders in the field of ‘cancer and work’ in the Netherlands, i.e., medical specialists in oncology, medical social workers, re-integration and vocational rehabilitation agencies, and the Dutch Cancer Patient Movement (Leven met Kanker Beweging) [22]. Finally, we conducted a focus group study with CSs with job loss and with insurance physicians, to identify barriers and facilitators for RTW specifically in CSs with job loss. For example, we discussed which barriers and facilitators CSs with job loss experience in their RTW after cancer. Also, we explored what a suitable duration and intensity level, in terms of frequency of appointments, would be for the intervention program, and in what way the intervention program and the study procedures could be implemented at the SSA. We used the results of the focus group study in the developmental process of the intervention program.

The intervention is consistent with the ‘Dutch Guideline of Oncologic Revalidation (Richtlijn Oncologische Revalidatie)’ [23] and includes elements of a participatory approach, in which the participant will be actively involved in the development, content and execution of his/her RTW plan. Specifically, the participant will be encouraged to actively participate in (1) developing his/her consensus-based tailored RTW plan, (2) coaching on identifying obstacles and creating possibilities for RTW, and (3) exploring possibilities for (therapeutic) return to an actual workplace. The first two steps (developing a RTW plan and coaching) will take place in the participant’s home or at a location nearby, and will be carried out by a re-integration agency, specialized in coaching and support of CSs regarding RTW. The third step (actual placement in a workplace) will be carried out by two job hunting agencies and the participants will travel to the nearest local office(s) of the agencies. The content of the tailored RTW intervention program is, to a certain extent, related to the attitudes-social influences-efficacy model [24]. That is, the first part of the intervention program, i.e., preparation for RTW, relates to behavioral determinants such as attitude and (self-) efficacy. The latter part of the program, e.g., removing barriers for RTW, relates to social influence by involvement of facilitating professionals in the RTW process.

